#### Follow-up

During the 4-week acupuncture-free follow-up, escape medication can be used under the same conditions as during the run-in period. If required for the eighth time, conventional treatment adjustments are proposed and documented.

#### Visit 10: end of study visit (t=14)

Four weeks after the final acupuncture session, an end-of-study visit is conducted. AEs are assessed, and weight/height is recorded.

#### Questionnaires and diaries

Patients complete questionnaires on treatment satisfaction, AE, PedsQL and school absence at specified visits. Symptom diaries are maintained daily from the run-in up to the follow-up visit (table 2).

**Table 2 T2:** Study procedures

	T=−2 Eligibility screening	T=0 Screening patient	T=2	T=4	T=6	T=8	T=10	T=14
Research visit (duration in minutes)	X (60)	X (30)		X (30)		X (30)		X (30)
Check for exclusion criteria	X	X						
Informed consent	X							
Rome IV criteria FC assessment	X	X		X		X		X
Acupuncture								
−1 sessions/week			X*	X*	X*			
−1 session/every other week						X*	X*	
Symptom diary	X†	X†	X‡	X‡	X‡	X§	X§	X¶
Adverse events								
Research nurse			X		X		X	X
Acupuncturist		X	X	X‡	X	X‡		
Questionnaires								
Quality of life		X			X		X	X
School absenteeism		X						X
Satisfaction with treatment					X		X	X

* Patients will receive eight acupuncture treatments during 10 weeks (one session per week during 6 weeks, followed by one session every other week during 4 weeks) between t=0 and t=10.

† Patients will fill out the symptom diary daily for the first 2 weeks.

‡ Symptoms over the prior week will be recorded weekly at each acupuncture session.

§ Symptoms over the prior 2 weeks will be recorded fortnightly at each acupuncture session.

¶ Symptoms over the prior 4 weeks will be recorded at the closing session.

FC, functional constipation.

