**Figure 1 F1:**
[figure not shown]
Schematic depiction of study design. Participants will receive eight acupuncture sessions over 10 weeks. At each session, symptoms and adverse events over the previous week will be recorded. Participants will complete surveys at five time points, including the validated PedsQL 4.0 Generic Core Scale and 3.0 Gastrointestinal Symptoms Scale and module, and questions monitoring adverse events, treatment satisfaction and school absence. After the baseline eligibility check, participants will visit the research nurse for five study visits, allowing for assessment of primary and secondary endpoints. The study visits at t=0, t=3, t=6 and t=10 will take place after the acupuncture sessions.

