#### Visit 3–9: acupuncture treatment

Patients receive eight acupuncture sessions over 10 weeks (one per week for 6 weeks, then one every other week for 4 weeks). Acupuncture sessions are conducted by one of two acupuncturists, with a physician or research nurse present. At each acupuncture session, the acupuncturist records the patient’s bowel habits, gastrointestinal symptoms and the use of escape medication during the period between sessions, based on the patient’s symptom diary. At weeks 3, 6 and 10, adverse events (AEs) are evaluated.

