#### Safety

Occurrence of AEs (needle-related pain, irritation, haematomas, headache, syncope, sedation, neuropathy) assessed at weeks 3, 6, 10 and 14. Severity and treatment relation will be recorded.

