#### Efficacy

Treatment success, defined as resolution of FC per Rome IV criteria at the end of the intervention (EOI).^3 37^ Rome IV criteria will be assessed by the investigator at the screening visit (visit 1) and at the EOI visit. For the EOI assessment, the criteria will be assessed over the last 4 weeks of the acupuncture intervention, or, in the event a participant discontinues the study prematurely within 4 weeks, over the intervention period. Other efficacy endpoints will be assessed via symptom diaries, the endpoints, including quality of life and school absence, are based on a previously published core outcome set^45^:

Defecation frequency (bowel movements/week).Stool consistency (Bristol Stool Scale).Painful defecation (yes/no).Faecal incontinence frequency (episodes/week).Withholding behaviour (yes/no).Abdominal pain (yes/no, Visual Analogue Scale score).Spontaneous bowel movements (>24 hours after escape medication).Time between acupuncture and defecation.Bowel movements <24 hours after acupuncture.Escape medication use and effect.

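### Table 2 omits the week-10 research visit and Rome IV assessment that the treatment-success definition and the Figure 1 legend require

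*Protocol article*

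**What the plan says.** The Efficacy section (Secondary outcomes) gives the endpoint: "Treatment success, defined as resolution of FC per Rome IV criteria at the end of the intervention (EOI"). It names the assessor and the occasions: "Rome IV criteria will be assessed by the investigator at the screening visit (visit 1) and at the EOI visit". It also fixes the period: for the end of intervention, "the criteria will be assessed over the last 4 weeks of the acupuncture intervention".

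The section on Visits 3–9 sets the length of treatment: "Patients receive eight acupuncture sessions over 10 weeks (one per week for 6 weeks, then one every other week for 4 weeks"). The Figure 1 legend says: "The study visits at t=0, t=3, t=6 and t=10 will take place after the acupuncture sessions".

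Table 2 (Questionnaires and diaries) marks the rows "Research visit (duration in minutes") and "Rome IV criteria FC assessment" at t=-2, 0, 4, 8 and 14. Both rows are empty at t=10.

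The Safety section has adverse events "assessed at weeks 3, 6, 10 and 14", and the section on Visits 3–9 gives weeks 3, 6 and 10. The research-nurse adverse-event row of Table 2 has t=2, 6, 10 and 14.

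**The concern.** Treatment success is the first-named efficacy endpoint and the only one for which the Statistical analysis section names a test (McNemar). The pilot is also meant to supply information for designing a randomised trial. A schedule table is what staff usually work from day to day, and this one shows no Rome IV assessment at the time point where the endpoint is defined.

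Two things could go wrong. The assessment could be left out at week 10, or the t=8 or t=14 assessment could be used in its place. The first comes before acupuncture has finished. The second follows the four weeks without acupuncture. Neither measures what the Efficacy section defines, and a missed investigator assessment cannot be fully rebuilt later.

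**Working it through.** The plan gives no figure to reproduce on this point. The check sets the places side by side and then measures the overlap of time windows.

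**When the intervention ends.** Treatment runs for 10 weeks. The footnote to Table 2 places the eight sessions between t=0 and t=10. The Visit 10 section puts the t=14 visit four weeks after the last session, and 14 − 4 = 10. So the end of intervention is t=10, and its last four weeks are weeks 6 to 10.

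**What is scheduled when.**

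| Item | Table 2 | Elsewhere in the article |
|---|---|---|
| Research/study visits after eligibility | 0, 4, 8, 14 (four) | Figure 1 legend: five, with 0, 3, 6 and 10 named; the Visit 10 section adds 14 |
| Rome IV assessment | -2, 0, 4, 8, 14 | Efficacy: visit 1 (t=-2) and the end-of-intervention visit |
| Nurse adverse-event check | 2, 6, 10, 14 | Safety: 3, 6, 10, 14; Visits 3–9: 3, 6, 10 |
| Quality of life | 0, 6, 10, 14 | Quality of life: 0, 6, 10, 14 (agrees) |

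The research-visit, Rome IV, diary, nurse and quality-of-life rows each split into eight cells against the eight-column header. The diary, nurse, quality-of-life and satisfaction rows all carry a mark at t=10. A column shift in text extraction is therefore an unlikely explanation for the blank.

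Table 2 is also at odds with itself. The Figure 1 legend has study visits conducted by the research nurse, yet the table's nurse checks at t=2, 6 and 10 fall where it shows no research visit.

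**Overlap with weeks 6 to 10.** For an assessment at week t looking back four weeks:

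overlap = max(0, min(t, 10) − max(t − 4, 6))

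- t=4: max(0, 4 − 6) = 0 of 4 weeks
- t=8: 8 − 6 = 2 of 4 weeks
- t=14: 10 − 10 = 0 of 4 weeks
- t=10 (not in Table 2): 10 − 6 = 4 of 4 weeks

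The article fixes a four-week look-back only for the end of intervention, so applying it at t=4, 8 and 14 is an assumption. The t=8 result does not depend on it: no look-back from week 8 can see weeks 8 to 10, so 2 of 4 is the ceiling. At t=14, a longer look-back could reach weeks 6 to 10 only by also taking in the four weeks without acupuncture.

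**What the diary can replace.** The diary is kept daily, and the reviews at t=8 and t=10 each cover two weeks, together weeks 6 to 10. The diary items listed under Efficacy correspond to about 4 of the 7 criteria in Table 1: frequency, retention (through withholding), painful or hard stools, and incontinence. The other 3 are not listed: large-diameter stools, stools that obstruct the toilet, and rectal faecal mass. A child meets the definition with two or more criteria, so:

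- two or more diary criteria met: failure is established;
- one met: a single unlisted criterion would make it a failure;
- none met: two of the three unlisted criteria would make it a failure.

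The diary items alone can show failure but cannot fully confirm success.

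**The case against.** A reader of Table 2 might infer that the endpoint is never collected, or that none of the 18 children has a scheduled assessment. The documents do not support that. The Efficacy section states the assessor, the occasion and the window, and the Figure 1 legend has a study visit at t=10. Table 2 itself has the child in contact at t=10 for acupuncture, diary review, the nurse's adverse-event check, quality of life and satisfaction. Staff who follow the text would collect the endpoint.

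The diary also covers the whole window, and the Visit 2 section already accepts diary information for judging the modified criteria at enrolment. Two of the three unlisted criteria are history items that can be asked about. That narrows the risk but does not remove it: rectal mass remains, and asking later is not the investigator assessment that was specified.

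The endpoint is secondary, in an uncontrolled feasibility pilot whose Statistical analysis section rules out efficacy claims. This stands and limits the weight of the point.

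The side issues are smaller still. Only children who meet the modified criteria after the run-in are treated, so all are positive at t=0 whichever visit is called baseline. Predefined adverse events are also collected by weekly questionnaire, so week 2 against week 3 matters little.

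**Conclusion.** Table 2 contradicts the Efficacy section and the Figure 1 legend on whether there is a research visit and a Rome IV assessment at t=10. The investigator-assessed treatment-success endpoint is at risk of being missed or of being taken at t=8 (at most 2 of the 4 required weeks) or t=14 (none, with a four-week look-back). The diary is a partial safeguard.

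This rests on the intervention ending at t=10, on the table's columns having been read correctly, and on the diary holding no more than the items listed under Efficacy; the diary form itself is not shown. How likely staff are to follow the table rather than the text cannot be judged from the article.

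The point is an error of consistency in an operational table. It does not touch the primary outcome of completion with attendance. It is still worth correcting promptly, because an assessment missed at week 10 cannot be fully recovered.

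**What to change.** - In Table 2, mark a research visit and an investigator Rome IV assessment at t=10, and state that it covers weeks 6 to 10.
- Reconcile the other research-visit weeks with the Figure 1 legend, and the nurse adverse-event weeks with the Safety and Visits 3–9 sections (weeks 3, 6, 10 and 14). Table 2 has no t=3 column at present.
- Add t=10 rather than simply moving t=8 to it. Moving would leave post-eligibility visits at 0, 4, 10 and 14, still one fewer than the five in Figure 1. The rules for sessions 5–8 also refer to persistent Rome IV criteria, so the sponsor should first confirm whether the t=4 and t=8 assessments serve that purpose.
- State whether the t=-2 or the post-run-in t=0 assessment is the baseline for the McNemar comparison.
- Recruitment was expected from June 2025, so some children may already have passed week 10. For each of them, record whether and when the end-of-intervention assessment was made.

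The cost is a corrected table, a note to study staff and, on the table's own duration for a research visit, about 30 minutes per child at t=10. No extra trip is needed, because the child already attends then for acupuncture.

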### Medication and co-interventions

Participants will continue their prestudy PEG dosage (≥0.2 g/kg/day) and non-pharmacological constipation treatments as previously prescribed by the medical team in charge. Concomitant use of laxatives other than PEG and other than escape medication (such as other osmotic or stimulating laxatives, eg, magnesium hydroxide, sodium picosulfate) is permitted if participants have been treated for at least 3 months prior to study initiation, as it is considered unethical to require discontinuation of such established therapy. The use and dosage of these co-medications will be documented. Current medication unrelated to defecation (eg, asthma medication) should be maintained. Initiation of new FC treatments or PEG dose increases during the intervention is prohibited. PEG dose reductions, if prescribed, will be documented. New medical treatments during the study will be assessed for impact, with potential withdrawal if necessary. Any PEG dose increase after the final acupuncture session will be recorded during follow-up.

### Escape medication

As is common in paediatric research settings, if a child does not defecate for 72 hours or experiences faecal impaction symptoms, escape medication (bisacodyl or enemas) will be given daily for up to a maximum of 3 days.^37 41 42^ If ineffective, the participant will be examined and withdrawn if faecal impaction is present. Dosage regimens adhere to the European Society for Pediatric Gastroenterology Hepatology and Nutrition^10^ and the Dutch Pediatric Formulary (https://www.kinderformularium.nl/) recommendations (box 1). Patients requiring disimpaction eight or more times during the intervention are considered treatment failures and will be withdrawn.

### Treatment

This study evaluates acupuncture administered by a certified acupuncturist using Seirin Pyonex press needles (0.2×0.3 mm for children <9 years, 0.2×0.6 mm for those ≥9 years) and 0.12–0.16×30 mm Seirin acupuncture needles (3B Scientific GmbH, Hamburg, Germany), all CE-certified (CE0123) medical devices used as intended. Acupuncture treatment combines four treatment techniques adapted to age: non-penetrating Shonishin techniques (stroking, pressing and tapping; online supplemental appendix 1), non-penetrating Tsumoshin technique (acupoint pressing; figure 2, online supplemental appendix 2), inserted needles with an applicator guide tube (minimising sensory stimulation) and Pyonex press needles (figure 2).

**Figure 2 F2:**
[figure not shown]
Acupuncture tools. Left, 0.14×30 mm Seirin acupuncture needle (above) and Seirin Pyonex press needle (below). Arrow points to 0.2×0.3 mm needle. Right, the Tsumoshin tool, a blunt-tipped non-penetrating needle with a rounded millet-seed-like point used for pressing the body surface.^15^

Patients are treated in both supine and prone positions, with acupoint selection based on age and acupuncturist evaluation. Treatment consists of standard and optional components (figure 3) and is discontinued if needle positioning poses a safety risk or if the child experiences excessive fear or stress. All patients are first treated with non-penetrating Shonishin and Tsumoshin techniques per traditional Japanese acupuncture principles (online supplemental appendices 1 and 2).^15^ Press needles are placed at BL-25 (Dachangshu) and TF-4 (behind the Ear ShenMen) in all sessions, with either ST-25 (Tianshu) or SP-15 (Daheng) selected based on acupuncturist’s evaluation (figure 4). Acupoints were selected based on literature and expert consensus.^16 34 36^

**Figure 3 F3:**
[figure not shown]
Acupuncture treatment decision tree according to age groups—session 1. All needles and press needles are placed bilaterally, unless stated otherwise. Shonishin: a Japanese non-penetrating treatment method using techniques of stroking, pressing and tapping, applied down the back and back of the legs, down the abdomen and anterio-lateral edges of the legs and down the arms.^15^ Tsumoshin: non-penetrating technique of acupoint pressing using the Tsumoshin tool, a blunt-tipped needle with a rounded millet-seed-like point used for pressing the body surface.^15^

**Figure 4 F4:**
[figure not shown]
Localisation of main acupoints targeted with (press-tack) needling at every acupuncture session. Pictures taken with patient consent for publication in a medical journal. Coloured dots (middle and right images) were added for schematic illustration. The press-tack needle placed at the Ear Shen Men (TF-4) on the posterior surface of the right auricle is highlighted with a black circle to enhance visibility.

Treatment progresses through an initial session (figure 3), followed by three sessions incorporating additional points (online supplemental figure 1) and four further expanded sessions (online supplemental figure 2), further detailed in the following section. Step-ups may be delayed or advanced based on clinical evaluation, with reasons documented. The acupuncturist may select optional acupoints relevant to defecatory issues, limited to a predefined set (figure 3, online supplemental file 1/2). These were determined through literature review and a survey of 39 experienced acupuncturists across Europe, Asia, Oceania and North America specialising in Shonishin/Japanese Meridian Therapy, with 29 providing input on techniques and acupoint selection. Standard and optional acupoint locations are detailed in figure 4, online supplemental appendix 3.

### Acupuncture

#### Session 1

All children receive non-penetrating Shonishin techniques (stroking, pressing, tapping) and a unilateral press-tack needle behind the ear at TF-4 (ShenMen) (figure 3). Light pressure is applied using Tsumoshin for one of four root pattern treatments, selected based on Traditional Japanese Medicine principles after history and examination (figure 3, online supplemental appendix 1). In children <9 years, treatment concludes with bilateral 0.3 mm Pyonex press-tack needles at BL-25 and either ST-25 or SP-15, left indwelling and replaced at the next session. In children ≥9 years, needling at BL-25 and ST-25 or SP-15 bilaterally is followed by 0.6 mm Pyonex press-tack needles at the same points, left indwelling and replaced at the next session. Press-tack needles dislocated >48 hours after placement or purposefully removed at any time are not replaced but documented.

#### Sessions 2–4

In children <9 years; before placing press-tack needles, BL-25 and ST-25 or SP-15 are needled bilaterally for 5 min using Seirin needles, followed by bilateral Pyonex press needles (0.3–0.6 mm) based on pain response and prior treatment (online supplemental figure 1). In children ≥9 years, two additional points (selected from LI-11, ST-27, SP-14, SP-6) are needled per session, totalling six needles (online supplemental figure 1).

#### Sessions 5–8

In children <9 years, additional needling (1–3 points) is introduced based on persistent Rome IV criteria for FC, selecting from LI-11, ST-27, SP-14 and SP-6 (online supplemental figure 2). Final sessions involve 5–7 needles. Five press-tack needles (0.3–0.6 mm) remain standard at BL-25, ST-25 or SP-15 bilaterally, and behind the ear at TF-4 unilaterally (figure 3C). In children ≥9 years, up to four additional points (TB-6, CV-12, KI-6, ST-36) are selected based on persistent Rome IV criteria for FC, increasing to a maximum of 10 needles in final sessions. Acupuncture points and rationale are documented per session. Five press-tack needles (0.6 mm) remain standard at BL-25, ST-25 or SP-15 bilaterally, and TF-4 unilaterally (online supplemental figure 2).

### Safety monitoring

Acupuncture is generally well-tolerated, with infrequent and mild AEs reported in paediatric studies.^16 43 44^

#### Risks and benefits

All participants will receive standard care in addition to acupuncture. Acupuncture is considered safe, with a ‘negligible risk’ classification according to the NFU (Dutch Federation of University Medical Centers) guidelines. No additional participant insurance is required as no additional risks are expected. Participants will receive free acupuncture treatment by certified acupuncturists, with reimbursement for travel and parking costs.

#### Adverse events

AEs are defined as any undesirable experience occurring to a subject during the study and considered related to acupuncture treatment. Predefined AEs—including needle-related pain, local irritation, haematomas, headache, syncope, sedation and neuropathy—will be assessed weekly via questionnaires. All AEs observed by the investigator or reported by participants will be documented, including severity (mild, moderate or severe) and relationship to treatment (unrelated, possibly, probably or definitely related). Given the nature of acupuncture, serious AEs are not expected.

AEs occurring from the first study-related procedure until 3 months postintervention will be recorded in the case report form and monitored until resolution or stabilisation. Follow-up may require additional tests, medical procedures or referral to a physician or specialist.

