#### Visit 1: eligibility check (t=−2)

Patients will be assessed for eligibility based on inclusion and exclusion criteria. Baseline data, including anthropometrics, will be recorded. Patients will receive instructions on defecation diaries and escape medication usage. A 2-week baseline run-in period follows, where participants continue PEG treatment (min. 0.2 g/kg/day). Children who meet the modified Rome IV criteria for FC (adjusted for the duration of the run-in period) will be enrolled to receive acupuncture (table 1).^3^

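### The adverse event definition requires relatedness to acupuncture, which contradicts the causality scale and recording window beside it; that window also runs 8–9 weeks past the last scheduled contact

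*Protocol article*

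**What the plan says.** The Adverse events section makes four statements that bear on each other.

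- Definition: "AEs are defined as any undesirable experience occurring to a subject during the study and considered related to acupuncture treatment".
- Documentation: "All AEs observed by the investigator or reported by participants will be documented".
- Causality grade: "relationship to treatment (unrelated, possibly, probably or definitely related").
- Window: "AEs occurring from the first study-related procedure until 3 months postintervention will be recorded in the case report form".

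The schedule is set elsewhere. At Visit 1, "A 2-week baseline run-in period follows". A bowel clean-out of 2–3 days then precedes the first session (Visit 2). In the treatment phase, "Patients receive eight acupuncture sessions over 10 weeks". Under Visit 10, "Four weeks after the final acupuncture session, an end-of-study visit is conducted", at t=14. The Study schedule section gives a total length of 16 weeks. Symptom diaries stop at the follow-up visit, and Table 2 has no later column.

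The safety outcome (Secondary outcomes, Safety) is the occurrence of seven listed event types, "assessed at weeks 3, 6, 10 and 14", with severity and relation recorded. The Statistical analysis section plans to report AE frequency.

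**The concern.** An AE definition decides what enters the case report form; causality is normally graded afterwards. Here the causality judgement is part of the definition, so an event judged unrelated need never be written down. The staff making that judgement know the treatment, and there is no control group to show the background rate.

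Some events that fall outside the definition still matter to a pilot in children. An untoward event in the run-in or clean-out happens under study procedures, but before acupuncture, so it cannot be related to acupuncture.

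Safety is a secondary objective, and the pilot is meant to inform an RCT. An event filtered out at recording cannot be restored at analysis. A recording period that extends beyond all planned contact also invites a reader to take the whole period as equally well observed.

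**Working it through.** **1. Definition against the causality scale.** The definition admits only events considered related to acupuncture. The scale has four grades, one of which is *unrelated*. Under the definition that grade is always empty; if it can be used, the definition is not being applied. The sentence on documenting all AEs does not settle this, because it uses the term just defined. Two readings remain:

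- The definition governs: unrelated events are excluded before grading, and AE frequency counts only events already judged related.
- The documentation sentence and scale govern: all events are recorded and graded, and nothing is filtered.

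The text does not say which applies.

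**2. Definition against the start of recording.** Recording opens at the first study-related procedure. The eligibility visit is at t=−2, and the clean-out also comes before session 1. No event in this stretch can be related to a treatment not yet given, so the window opens over a period in which the definition admits nothing.

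**3. Definition and schedule against the end of recording.** The plan's own duration reproduces: 2 weeks run-in + 10 weeks intervention + 4 weeks follow-up = 16 weeks, from t=−2 to t=14.

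The article does not convert 3 months to weeks. I take 12–13 weeks, counted from week 10, and start the window at t=−2.

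| | 12 weeks | 13 weeks |
|---|---|---|
| Window closes | 10 + 12 = week 22 | 10 + 13 = week 23 |
| Weeks after last contact | 22 − 14 = 8 | 23 − 14 = 9 |
| Whole window | 22 + 2 = 24 weeks | 23 + 2 = 25 weeks |
| Share of whole window | 8/24 = 33% | 9/25 = 36% |
| Share of post-intervention part | 8/12 = 67% | 9/13 = 69% |

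The definition also confines AEs to the study period, which ends at week 14, so weeks 14 to 22–23 lie inside the recording window but outside the definition.

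**4. Endpoint against the gap.** The safety outcome is assessed at weeks 3, 6, 10 and 14. All four fall at or before the last contact, so the late gap removes nothing from this endpoint.

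**5. Assessment weeks.** The Visit 3–9 section has AEs evaluated at weeks 3, 6 and 10, and the Safety outcome uses weeks 3, 6, 10 and 14. Table 2 marks the research nurse's AE check at T=2, 6, 10 and 14, and has no T=3 column. The first nurse check is therefore week 2 in one place and week 3 in two others.

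**The case against.** The strongest reply is that under-counting is assumed. The section says all AEs will be documented and provides an *unrelated* grade; if staff follow those sentences, nothing is lost. This stands to the extent that the provable defect is a contradiction and the loss is conditional. It does not remove the problem, because applying the definition as written does filter events.

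A reader might infer that the safety endpoint as such is under-counted. The documents do not support that. The endpoint has its own list of event types, solicited by questionnaire, and its own assessment weeks, all within scheduled contact.

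A reader might also infer that nothing is ascertained after week 14, or that this stretch would be reported as free of events. The article says neither. Participants' reports are accepted, so passive reporting continues, and a condensed article may leave the handling of late reports to the full protocol. The 33–36% is calendar time without scheduled contact, not a share of events lost.

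It is tempting to add that zero events in 18 children would still allow a true rate of up to 1 − 0.05^(1/18) = 15.3% (one-sided 95%). That is correct arithmetic, but it holds with or without a filter and says nothing about missed events.

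The AE schedule could be read as three rival versions. It is partly two layers: checks by the acupuncturist at sessions, and separate evaluations at set weeks. The week 2 versus week 3 mismatch for the nurse remains.

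Finally, judging causality unblinded and without a control is inherent in an open-label single-arm pilot, and the lack of a control group is disclosed. That stands, and it is a reason not to let the judgement decide what is recorded.

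**Conclusion.** The point holds as an internal contradiction with a conditional consequence. The definition is incompatible with the *unrelated* grade, with recording that opens before any acupuncture, and with recording that continues after the study has ended. If the definition is followed, events judged unrelated go unrecorded and overall AE frequency can be too low. How much too low cannot be computed, because the article gives no AE rates.

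The stated window exceeds scheduled contact by about 8–9 weeks, or 33–36% of its length, assuming that 3 months is 12–13 weeks and that recording starts at t=−2. That gap weakens the promise to record to 3 months; it does not touch the week 3–14 endpoint. The definition deserves correction first, because a filter at recording is irreversible. The window and the nurse's assessment week are alignments that belong in the same amendment.

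**What to change.** 1. Delete the closing clause of the definition that makes relatedness to acupuncture a condition. Record every untoward event from the first study procedure, then grade severity and relation, so that the *unrelated* grade has content.
2. Report all events and, as a subset, those possibly, probably or definitely related.
3. Reconcile the window with the last contact. Either end systematic AE reporting at week 14 and label anything later as passively reported, or add one brief remote AE query to all participants at 3 months. The second option would be a new contact: the follow-up by online questionnaire that the article describes is for withdrawn participants. Bring the definition's restriction to the study period into line with whichever is chosen.
4. Use one week for the nurse's first AE assessment in Table 2, the Visit 3–9 section and the Safety outcome.

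Recruitment was expected to start in June 2025, so the report should also say which reading was applied to children treated before the change.

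The cost is an amendment to the wording, slightly more AE recording and, under the second option in item 3, one short remote contact per child. Sample size and the primary outcome are unchanged.
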